**Methods::**

This observational trial will at first diagnose the pattern identification types of lung cancer patients with BCQ assessment and then elucidate their relationships with proteomics. Blood samples will be collected before surgery along with clinical information of participants. The patients’ pattern identification in TKM will be diagnosed from BCQ assessment. Then, lung cancer patients will be divided and pooled into 3 lung cancer entire (LCE) groups according to their pattern identification types (Xu, Stasis, or Gentleness). Three lung cancer representative (LCR) groups will be selected and pooled from each LCE group by selecting those with the same control factors. The 3 LCE groups and the 3 LCR groups from lung cancer patients will be independently analyzed through the glycoproteomics approach based on the patients’ pattern identification. Glycoproteins from the 6 groups will be identified through proteomics approach and then categorized for analysis.

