#### Representative groups

2.7.3

The LCR groups will be generated from each LCE group by applying the selected control factors to lung cancer patient samples. The selected samples from LCEX group will be included in the lung cancer representative Xu (LCRX) group. Likewise, the selected samples from LCES group will be assigned to the lung cancer representative Stasis (LCRS) group while samples from LCEG group will be included in the lung cancer representative Gentleness (LCRG) group. The representative samples must be selected to have the same numbers of samples in each control factor for all pattern identification groups. It is also crucial to select a sufficient number of samples in order to reflect each pattern identification group. The number of patients with each control factor will be kept constant in each representative group.

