#### Scientific validation of entire groups using representative groups

2.7.4

Comparison of the identified glycoproteins between the LCE groups and the LCR groups with the same pattern identification type may reveal whether each LCR group truly represents each LCE group. This will be used to validate the unique glycoproteins from each pattern identification type of lung cancer patients under the framework of TKM.

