### Statistical analysis with database searches

2.13

After at least 2 MS/MS data are obtained from each sample, protein identification will be performed with 2 complementary database search programs. Both Proteome Discoverer 1.4 (Thermo Fisher Scientific Inc., USA) and ProteinPilot 5.0 (SCIEX, USA) will be used to identify proteins from MS and MS/MS spectra. Each software program has its own unique analysis algorithm. Thus, it will be meaningful to compare the results from the 2 programs because it will reinforce the confidence of the identified proteins. At least 4 data files with identified proteins will be produced from each sample. Each data file will be individually sorted and filtered under the following conditions:

(1)dynamic modification option: deamidated (N-glycosylation)(2)peptide confidence levels: the peptide is significant only if (a) confidence levels are over 95%, or (b) confidence levels are below 95% in 2 runs but show significant MS/MS spectra.(3)proteins inclusion and exclusion: for Proteome Discoverer software, only the proteins with protein scores of 6.0 or higher will be included; for ProteinPilot software, only the proteins with the unused values of 2.0 or higher will be included. The rest of the identified proteins will be excluded from the results.

Starting with the significant data from the 2 software programs, only the peptides/proteins with N-glycosylation sites will be selected and used for the parent protein identification. These glycoproteins will be sorted and compared within each group (Xu, Stasis, and Gentleness). Then these proteins will be sorted into those that are identified in all LCE groups, all LCR groups, and only certain group(s). The resulting 6 N-glycoprotein lists will be used for the following 5 comparative analyses:

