(1)the glycoprotein comparison sets from the first and second MS/MS runs for the confirmation of reproducibility(2)the glycoprotein comparison sets from the 2 protein search engines to increase the confidence level of identified proteins(3)the glycoprotein comparison sets between LCE groups and LCR groups to check the representativeness(4)the unique and intersection glycoproteins set by comparison of LCE groups (LCEX, LCES, and LCEG) based on their pattern identifications assessed from BCQs of the lung cancer patients(5)the unique and intersection glycoproteins set by comparison of LCR groups (LCRX, LCRS, and LCRG) based on their pattern identifications assessed from BCQs of the lung cancer patients.

The overall data processing and analysis procedures are described in Figure 2. Unique glycoproteins from each group with each pattern identification of lung cancer patients will be generated from the results.

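### Pattern-unique glycoproteins are defined within the LCE or the LCR set alone, so a protein can stay on the Xu-unique list although the trial's own Stasis subset contains it

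*Protocol article*

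**What the plan says.** The plan has six pooled plasma samples: three patterns (Xu, Stasis, Gentleness) in two tiers, the entire groups (LCE) and the representative groups (LCR).

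- **Nesting.** Section 2.7.3 forms each LCR group by selection from the LCE group of the same pattern; for Stasis, "the selected samples from LCES group will be assigned to the lung cancer representative Stasis (LCRS) group".
- **Uniqueness.** Section 2.13 item (4) derives "the unique and intersection glycoproteins set by comparison of LCE groups (LCEX, LCES, and LCEG". Item (5) derives "the unique and intersection glycoproteins set by comparison of LCR groups (LCRX, LCRS, and LCRG". Each uses three of the six lists.
- **Cross-tier comparison.** Item (3) is "the glycoprotein comparison sets between LCE groups and LCR groups to check the representativeness". Section 2.7.4 gives its scope: "Comparison of the identified glycoproteins between the LCE groups and the LCR groups with the same pattern identification type". It also gives its use: "This will be used to validate the unique glycoproteins from each pattern identification type of lung cancer patients".
- **Sorting step.** Before the five comparisons, section 2.13 states: "Then these proteins will be sorted into those that are identified in all LCE groups, all LCR groups, and only certain group(s".

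The output is a set of unique glycoproteins for each group. The Discussion intends the proteins identified for each pattern to serve as pattern indicators (biomarkers). Protein identification and categorization by pattern is primary outcome 3 in section 2.2.1.

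**The concern.** Calling a protein unique to Xu asserts that it is absent from Stasis and Gentleness. In this plan, absence means that the protein did not pass the identification filters in one pooled sample per group, and non-identification is weak evidence of absence. The nested LCR pools give a second look at plasma from some of the same patients, so they can show that a presumed absence was a missed detection.

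Items (4) and (5) do not use that second look. A protein can meet the written definition of Xu-unique in one tier while the other tier identifies it in Stasis patients. At stake is whether the unique lists, which are the study's main product and its source of candidate indicators, are consistent with all six lists the study produces.

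**Working it through.** **1. One protein followed through the written rules.** Suppose it is identified in LCEX and LCRS and not in LCES or LCEG.

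- Item (4): present in LCEX, absent from LCES and LCEG, so Xu-unique.
- Item (3), LCEX against LCRX: this pair cannot show presence in Stasis. If LCRX also identifies the protein, the pair appears to confirm the Xu claim.
- Item (3), LCES against LCRS: a discordance appears. Its stated bearing is on how well LCRS represents LCES. No rule carries it over to the Xu list.
- Item (5): if LCRX and LCRG both miss the protein, it is Stasis-unique in the LCR tier while being Xu-unique in the LCE tier.

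All LCRS patients belong to LCES, so on the trial's own identification criteria the protein is present in plasma of patients classed as Stasis. No stated step removes it from the Xu list.

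**2. How often this could happen.** The document gives no detection rate and no figure to reproduce. Assume a protein truly present in all six pools, identified in each with probability d.

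- Chance that item (4) calls it unique to some pattern: u = 3d(1 − d)². For Xu alone it is one third of this; at d = 0.5, 0.5 × 0.5² = 12.5%.
- Let r be the chance that an LCR pool identifies the protein when the LCE pool of the same pattern missed it. The share of these false calls contradicted by at least one of the other two patterns' LCR lists is 1 − (1 − r)².
- If pools are independent, r = d. If detection in the two tiers of a pattern shares a latent normal correlation of 0.5, r is 0.075, 0.205, 0.333, 0.477 and 0.676 at the five values of d below.

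| d | u | Contradicted, independent | Contradicted, correlation 0.5 |
|---|---|---|---|
| 0.1 | 24.3% | 19% | 14.5% |
| 0.3 | 44.1% | 51% | 36.7% |
| 0.5 | 37.5% | 75% | 55.6% |
| 0.7 | 18.9% | 91% | 72.7% |
| 0.9 | 2.7% | 99% | 89.5% |

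Example at d = 0.7: u = 3 × 0.7 × 0.3² = 18.9%. Contradicted if independent: 1 − 0.3² = 91%. With correlation 0.5: 1 − (1 − 0.477)² = 72.7%. At correlation 0.8 the shares for d = 0.5, 0.7 and 0.9 fall to about 37%, 50% and 68%.

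**3. What a cross-tier rule would leave.** Multiply u by one minus the contradicted share.

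- Independent, d = 0.5: 37.5% × 0.25 = 9.4%. At d = 0.7: 18.9% × 0.09 = 1.7%.
- Correlation 0.5, d = 0.5: 37.5% × 0.444 = 16.7%. At d = 0.7: 18.9% × 0.273 = 5.2%.

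The rule reduces false-unique calls but does not remove them. The contradicted share therefore understates how many such calls there are.

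**The case against.** The strongest reply is that the tiers are not judged in isolation. Section 2.7.4 says the cross-tier comparison will validate the unique proteins, and the LCES–LCRS pair in item (3) would show exactly the discordance described. That stands. A reader might infer that the plan has no cross-tier check, or throws this information away; the documents do not support either. What is missing is a link from that discordance to another pattern's unique list.

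A second reply is that the sort into proteins found only in certain groups might already do the work. Figure 2, which is said to describe the full procedure, is not available here, so this cannot be excluded. In the text, however, items (4) and (5) each name three groups of one tier as the basis for uniqueness.

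A third reply is that reconciling discordant sets is detail for a fuller document. This would hold if the article were silent on how uniqueness is determined. It is not silent: it fixes the comparison sets, and as fixed they permit the contradiction.

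Two further limits are fair. A reader might suppose that LCES misses proteins because it is a more dilute pool, but the document gives neither LCR sizes nor pooled volumes, and the calculation uses no dilution effect. The study also calls itself preliminary and lists biomarker discovery in a large population as a long-term outcome, which limits the immediate harm.

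**Conclusion.** The point holds in a bounded form. Uniqueness is defined within one tier, LCR is nested in LCE, and the cross-tier validation is described for same-pattern pairs without a consequence for another pattern's list. A protein that the trial itself finds in Stasis plasma can therefore remain Xu-unique under the written rule.

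That conclusion rests on the text and needs no numerical assumption. Its size does. For proteins common to all pools, the false-unique rate in the LCE tier runs from 2.7% to 44.1% over d = 0.1 to 0.9. The part that the other patterns' LCR lists would reveal runs from 19% to 99% if pools are independent, and from 14.5% to 89.5% at correlation 0.5. Detection probability, equal detection across pools and the correlation are all illustrative assumptions. It would be tempting to read the observed discordant share as the false-unique rate. It is only a lower-bound indicator, since some false calls go uncontradicted, and it also presumes that the contradicting identifications are correct.

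**What to change.** Change items (4) and (5) of section 2.13, and align section 2.7.4:

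- Report a glycoprotein as pattern-unique only if it is identified in none of the LCE and LCR pools of the other two patterns.
- List proteins that are unique within one tier but found in another pattern's pool of the other tier separately as discordant, rather than deleting them. For LCR-unique proteins, note that detection in another pattern's LCE pool may reflect factors controlled only in the LCR selection.
- Report discordant proteins as a share of all tier-unique proteins, labelled as a lower-bound indicator of false-unique calls and not as their rate.
- Use item (3) to count proteins found in an LCR pool but not in its own LCE pool, as missed detections.

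The cost is one further set comparison of six lists that already exist, plus protocol wording; no new samples or instrument runs are needed. The unique lists become shorter, and a false identification in another pattern's pool can move a real difference to the discordant list. That is why the discordant list should be shown in full.

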#### Control factors

2.7.2

Glycoproteins in blood can vary qualitatively and quantitatively by numerous variables such as sex, age, and medical history. The glycoproteins must be qualitatively and quantitatively analyzed based on the pattern identification of the lung cancer patients. We hypothesize that each pattern identification of TKM as well as other variables such as sex, age, medical history, and etc. affects glycosylations on plasma proteins. Therefore, all the other variables other than pattern identification must be strictly controlled.

Since it is impossible to control all of the 19 variables of clinical information, we need to select as many variables as possible that are within our control. For example, smoking can be selected as the control factor that is closely related to lung cancer while sex ratio and average age can be considered as basic control factors for qualitative and quantitative analysis of glycoproteins. Both TNM stage and cancer subtype can be selected as control factors. Disease histories can be selected as control factors that can affect glycosylation in cancer plasma. Patients with no prior history of cancers other than lung cancer will be selected because other cancers may affect the aberration in the glycan moieties of glycoproteins in the plasma. Cancer histories from direct family can be considered as a genetic factor.

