### Trypsin digestion and deglycosylation with PNGase F

2.11

The selected proteins will be digested with sequencing grade trypsin for protein digestion and then with PNGase F for deglycosylation of glycoproteins. The detailed proteomics method will follow the method section of the reference paper.^[44]^ The PNGase F-treated peptide mixtures will be stored at −80°C until analyses.

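### The pattern comparisons use only presence or absence in identification lists, although 2.7.2 requires quantitative analysis as well, so chance non-detection can make a glycoprotein look unique to a pattern

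*Protocol article*

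**What the plan says.** Section 2.7.2 (Control factors) sets the requirement: "The glycoproteins must be qualitatively and quantitatively analyzed based on the pattern identification of the lung cancer patients". It hypothesises that pattern, among other variables, affects the glycosylation of plasma proteins, and it presents sex ratio and average age as "basic control factors for qualitative and quantitative analysis of glycoproteins".

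Section 2.13 then fixes the analysis. Peptides and proteins are filtered by confidence and by hard protein-score cut-offs (6.0 in one search program, 2.0 in the other). Proteins are "sorted into those that are identified in all LCE groups, all LCR groups, and only certain group(s"). Then: "The resulting 6 N-glycoprotein lists will be used for the following 5 comparative analyses". Items 4 and 5 are the two that address pattern. Item 4 is "the unique and intersection glycoproteins set by comparison of LCE groups (LCEX, LCES, and LCEG") and item 5 is "the unique and intersection glycoproteins set by comparison of LCR groups (LCRX, LCRS, and LCRG"). The stated output is the set of glycoproteins unique to each pattern group. No listed comparison uses intensity, spectral count or any other measure of amount.

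Three other provisions bear on this:

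- Under 2.9 there is one pool per group, six in all.
- Section 2.7.4 says that comparing LCE with LCR groups will serve to validate the unique glycoproteins. Under 2.7.3 the LCR samples are drawn from the LCE groups.
- Section 2.12 promises more than two runs per sample, whereas 2.13 and the Figure 2 caption promise two or more.

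**The concern.** In an identification experiment, a protein missing from a list may be absent from the plasma, or it may be present and not picked up in that run, or have scored just under a cut-off. The set comparisons in 2.13 treat these cases alike. Two consequences follow.

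First, proteins detected unreliably will sometimes appear in one pool and not the other two by chance, and will then be reported as belonging to a pattern. The Discussion intends the identified proteins to serve as pattern indicators, so false entries would be carried forward as biomarker candidates.

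Second, the hypothesis concerns changes in glycosylation. The digest is treated "then with PNGase F for deglycosylation of glycoproteins" (2.11), so glycan structure is not read directly. The amount of each protein captured by the lectin column is an important remaining trace of a glycosylation change, and list membership discards it. The Introduction's own supporting example is a single serum protein whose glycosylation differed between disease types. Such a protein, if identified in all three pools, would be filed under intersection.

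**Working it through.** The article gives no detection rate, error rate or effect size for the pattern comparison, so there is no figure of its own to reproduce. The check asks how often a protein with no pattern effect would be called unique.

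**Inputs from the article:** three pools per comparison (2.13, items 4 and 5); two or more runs (2.13), or more than two (2.12).

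**Assumptions:** each run of each pool detects the protein with the same probability d, independently. A pool lists the protein if any run detects it; 2.13 does not state how runs are merged. Because d is not given, a range is shown.

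**Formulas:** with r runs, a pool lists the protein with probability q = 1 − (1 − d)^r. It is unique to exactly one of three pools with probability 3q(1 − q)². It is unique to the same pattern in both LCE and LCR, if detection in the two sets is independent, with probability 3[q(1 − q)²]².

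Example at d = 0.5 with two runs: q = 1 − 0.25 = 0.75, and 3 × 0.75 × 0.0625 = 0.141.

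| d | q, 2 runs | Unique, 2 runs | q, 3 runs | Unique, 3 runs | Same call in LCE and LCR, 2 runs |
|---|---|---|---|---|---|
| 0.3 | 0.51 | 36.7% | 0.657 | 23.2% | 4.5% |
| 0.5 | 0.75 | 14.1% | 0.875 | 4.1% | 0.7% |
| 0.7 | 0.91 | 2.2% | 0.973 | 0.2% | 0.02% |
| 0.9 | 0.99 | 0.03% | 0.999 | <0.001% | <0.001% |

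**Listing only when both runs agree.** Here q = d², and the same formula gives 22.4%, 42.2%, 38.2% and 8.8% at d = 0.3, 0.5, 0.7 and 0.9. A stricter listing rule alone makes matters worse from 0.5 upwards, because it also creates more apparent absences.

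**Detection that varies between proteins.** If d is spread evenly from 0 to 1 (mean 0.5), the any-run rule with two runs gives 17.1 false unique calls per 100 proteins, against 14.1 if all had d = 0.5. If d follows a Beta(4,1) distribution (mean 0.8), it gives 2.9 per 100, against 3 × 0.96 × 0.04² = 0.5% if all had d = 0.8. An average detection rate therefore understates the problem in these cases.

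**A strict two-sided rule.** Suppose a protein is unique only if found in both runs of one pool and in none of the four runs of the others. The chance is 3d²(1 − d)⁴, which is 6.5%, 4.7% and 1.2% at d = 0.3, 0.5 and 0.7. Requiring the same call in LCE and LCR, again assuming independence, gives 3[d²(1 − d)⁴]², about 0.14%, 0.07% and 0.005%.

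**The case against.** The strongest reply is that 2.13 is not without safeguards. It compares runs and search engines, and 2.7.4 uses the LCE-versus-LCR comparison to validate unique proteins. The two sets are separate pools with separate runs, so agreement between them would remove most chance misses, as the last column of the table shows. This stands as a reason not to quote the single-comparison percentages alone. It does not close the gap: nothing in 2.13 or 2.7.4 says a protein must pass any of these comparisons to be called unique. And because LCR patients come from LCE, agreement guards against random non-detection but not against differences in which patients make up the pools.

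A second reply is that the sentence in 2.7.2 explains why factors are matched, that the stated outcomes are identification and categorisation, and that the trial is preliminary. List comparison does fit those outcomes. But 2.7.2 states a requirement, and the enumerated analyses do not meet it. Figure 2 is not shown, and laboratory methods are deferred to reference papers, so abundance data may exist; no stated comparison uses them.

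A reader might also infer that the plan is blind to the hypothesised effect. The documents do not support that. Section 2.13 searches for deamidation as the mark of N-glycosylation and keeps only peptides or proteins with such sites, so site-level information survives the enzyme step, and a large enough change could still alter list membership.

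**Conclusion.** The point holds as a mismatch between 2.7.2 and 2.13 and as an undefined criterion for the main output. The mismatch can be read directly from the text.

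The size is not determined by the article. Under the stated assumptions (equal independent detection, two runs, any-run listing, one three-pool comparison) a false unique call has a chance of about 37% at d = 0.3, falling to 0.03% at d = 0.9. With three runs the figures at 0.3, 0.5 and 0.7 are about 23%, 4% and 0.2%. The problem is negligible for reliably detected proteins and concentrates near the score cut-offs.

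A reader might infer that a known share of the unique list will be false. That cannot be said, because neither the detection rates nor the rule for merging runs is given, and the LCE-versus-LCR comparison would cut the share sharply if it were made binding.

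**What to change.** Change 2.13 as follows.

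1. Add a label-free quantitative comparison (MS1 intensity or spectral counts) of each identified glycopeptide across all pools, from the runs already planned. Report it as descriptive fold differences. State that, with one pool per group, run-to-run variation is technical only and does not support inference about patients. Testing fold differences against it would let ordinary differences in pool composition pass as pattern effects. Sub-pools would address this but need extra runs.
2. Call a glycoprotein unique only if it is identified in every run of one pool, with no identification and no MS1 signal in any run of the other pools, and the same call is made in both the LCE and the LCR sets.
3. Beside each unique count, report the number expected from the run-to-run disagreement that comparison (1) already yields. Compute it under the same rule and let detection differ between proteins.

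The number of runs in 2.12 and 2.13 should be reconciled at the same time, since it drives the non-detection rate.

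The cost is some reprocessing of raw files and shorter unique lists, with no extra samples or runs. This assumes that the raw files retain usable MS1 signal, which the article does not describe. If they do not, spectral counts can serve for item 1, and the MS1 condition in item 2 would have to be dropped.
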